### Research governance

Approval and support for this study has been obtained from the following bodies: the National Research Ethics Service (reference 12-YH-0471) and the sponsor, North Cumbria University Hospitals NHS Trust. Contact person for the sponsor is the R&D director, [name]. There is no provision made for non-negligent liability; the CI and other research team members are covered by standard NHS indemnity. The study is funded by a Nurse Research Grant from the International Glaucoma Association, based on the ethically approved study protocol (version 1, 19 September 2012) and supporting study documents (i.e. patient information sheet, consent form, ‘glaucoma personal record’) [16].

### Publication and data-sharing policy

The study results will be presented at (inter)national scientific meetings and at local seminars and conferences. The results from the study will be written up and submitted to a peer-reviewed journal. We intend to write a summary sheet for distribution in, e.g., ophthalmology waiting areas. This summary sheet can also be distributed to participants upon request. All published data will not contain information that can identify any of the subjects who have participated in the study, in line with the Data Protection Act [17]. Each participant will be given a study number so that the data can be pseudoanonymised.

## Discussion

The NICE Guideline Development Group published recommendations for research into the clinical effectiveness of providing people with COAG with a ‘glaucoma personal record’ when compared with standard treatment [8]. To the authors’ knowledge, the HOPE Glaucoma study constitutes the first effort towards fulfilling NICE recommendations and the planned publication of study findings in circa 2017 will provide the first data generated by a randomised controlled trial on ‘glaucoma personal record’ provision. Findings will strengthen the evidence base available for glaucoma management guideline development and may have a positive impact upon the future education and care of glaucoma patients.

Strengths of the trial include the use of a time-matched control, the random allocation of the ‘glaucoma personal record’, allocation concealment to minimise selection bias, long-term recruit follow-up (36 months) and the use of validated questionnaires to capture outcome data. Due to its fairly pragmatic approach, the trial is not without limitations. The decision not to collect detailed data on patient co-morbidities could omit potential confounding factors throughout this trial. Other foreseeable study limitations include a limited patient demographic, due to recruitment from a single-centre in a rural location with a limited ethnic variety. The generalisability of trial findings may also be limited by the selection of participants from a nurse-led clinical nurse specialist new glaucoma referral clinic only. Gray et al*.* [9] indeed found that the depth of information provided for newly diagnosed patients varied across clinics and between individual clinicians. Despite this limitation, the use of one glaucoma practitioner throughout the duration of the trial offers a means of standardising the type and quality of information and materials given to all participants at diagnosis and during follow-up review. Variability in the nature of the information provided at diagnosis and in the quality of outcome measure assessment will be minimised, as the CI will be responsible for the provision and adaptation of care for all participants, according to the individual clinical need, and regardless of the arm to which they were allocated.

One other limitation of the trial includes the risk of bias. Due to the nature of the intervention - provision of a booklet - it is not feasible to mask participants to which arm of the study they will be allocated to. The CI is responsible for determining the suitability of participants, allocating the intervention and collecting data for the outcome measures in this trial, which introduces other sources of potential bias. The outcome assessor will not be masked to the interventional group, as the assessor distributed the ‘personal glaucoma record’ and clients will return with (or refer too) their record at follow-up; this increases the risk of detection bias. However, the utilisation of a second outcome assessor was deemed unworkable, and a pragmatic approach with one assessor was adopted.

The use of a ‘glaucoma personal record’, such as the one produced for this trial, for those diagnosed with OHT, SG and/or COAG may provide an additional, low-cost source of information to patients and other ophthalmic healthcare professionals which is easily produced and administered. Glaucoma personal records may have the potential to improve patients’ understanding of their condition, help reduce patient uncertainty and potentially improve medication adherence [18].

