**Methods/Design:**

HOPE Glaucoma is a 3-year, prospective, parallel-group, pragmatic, single-centred, randomised controlled trial. An anticipated 122 adults, newly diagnosed with glaucoma (including ocular hypertension, suspected glaucoma and/or chronic open-angle glaucoma) will be recruited from a nurse-led ophthalmology outpatient clinic at a medium-sized NHS Trust. Participants will be randomly allocated to receive standard clinical care (control arm) or standard care plus a glaucoma personal record, detailing the current state of their condition (interventional arm). Participant assessments are designed to test whether provision of a glaucoma personal record 1) improves patient knowledge of glaucoma and 2) contributes to improvements in clinical outcomes, i.e. delay of visual field loss. The primary outcome measure is better client knowledge of glaucoma at the 9–12 month follow-up visit. Secondary outcome measures include the rate of visual field loss and patient-reported outcome measures on visual function (National Eye Institute VFQ – 25) measured at baseline, 9–12 months, 24 months and 36 months. Estimating a 20 % drop-out rate, the study will have 90 % power to detect a mean two-point difference in glaucoma knowledge score between groups at 5 % significance - based on two-sided Mann–Whitney *U* test.

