### Sample size

The anticipated patient sample size of 122 will be recruited over a 12-month period. Power calculations for sample size, 90 % power and 5 % significance, based on two-sided Mann–Whitney *U* test for the primary outcome measure, patient knowledge of glaucoma. A priori power calculations, using GPower 3.1 software, result in the following sample sizes summarized in Table 2. The calculation also takes into account a 20 % drop-out rate over the initial 9–12-month follow-up period before patients return for their regular glaucoma follow-up and knowledge questionnaire visit.

**Table 2 Tab2:** Sample size calculation

Mean score control group (± SD)	Mean score intervention group (± SD)	Required total sample size, n
7 (3)	8 (3)	400 (200 per group)
7 (3)	9 (3)	122 (61 per group)
7 (3)	10 (3)	58 (29 per group)

*SD* standard deviation

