### Randomisation

Each participant will be assigned to the control or interventional arm by a pragmatic randomisation approach; there will be no stratification and randomisation will take place on a 1:1 ratio without blocking. Online freeware will be used to generate a random allocation sequence in advance of the recruitment period, seen only by the trial administrator (who will not be involved with data collection) [9]. Allocation concealment will be achieved using consecutively numbered, sealed, opaque envelopes prepared in advance of recruitment by the trial administrator. This will ensure the investigator is not aware of the allocation sequence in advance of randomization. Eligible subjects will be randomised and - if assigned to the intervention arm - presented with their glaucoma personal record by the CI immediately after written informed consent has been obtained. For overview of the study process, see Fig. 1.

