### Intervention description

Both groups will have exposure to current educational resources and materials presented at diagnosis, as is standard clinical practice. This may include an enlarged model of the eye, ocular anatomy posters, ocular coherence tomography sample scans, images of healthy and damaged optic nerve heads, examples of normal visual field tests and those showing glaucomatous loss, and a glaucoma information leaflet to take away with them. The chief investigator’s contact number will also be provided, as would be standard in her capacity as clinical nurse specialist in ophthalmology.

Those participants allocated to the interventional arm will, in addition to standard clinical care, be provided with their own ‘glaucoma personal record’ (Additional file 1), which will be personalised to document the current state of each participants’ glaucoma diagnosis and utilised during ophthalmologic review. Both groups of participants will be asked to complete the National Eye Institute Visual Functioning Questionnaire – 25 (VFQ-25) to gain an insight into patients’ perceptions about the impact that glaucoma may have on their daily living. The ‘glaucoma personal record’ will be administered to those participants randomised to receive the intervention by the CI immediately after the informed consent process has been completed.

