### Outcome measures

#### Primary outcome

The primary outcome measure is client knowledge of glaucoma, quantified using a validated researcher-conducted survey at 6–12 months post-recruitment [8], see Table 3. This survey and scoring system was used, and validated by ophthalmic colleagues in 2009/2010 “to establish the impact of educational support on clients’ knowledge of glaucoma and adherence, in preparation for a further interventional study” [9]. It provides an ordinal score of participants’ knowledge. The primary outcome measure is therefore the degree of understanding and knowledge retention of their OHT, SG, or COAG in the interventional group compared with the control group. Patients requiring ocular antihypertensive treatment at first presentation are eligible for inclusion in this trial; the total knowledge score achievable is either 12 for those not prescribed antihypertensive drops, or 17 for those prescribed eye drops during the course of the study. The survey will be administered by the CI when participants attend a ‘glaucoma review’ outpatient clinic between 6 and 12 months post-recruitment.

**Table 4 Tab3:** Overview of study timeline and outcome measures

Baseline	Baseline	9–12 months	24 months	36 months
Patient knowledge		X		
Patient perspective (VFQ-25)	X	X	X	X
Clinical parameters	X	X	X	X

*VFQ-25* National Eye Institute Visual Functioning Questionnaire – 25

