### Data collection and monitoring

Participant follow-up will be 3 years. The estimated primary completion date is September 2015 and the estimated study completion date is September 2017. An overview of the study timeline and recorded outcome measures are detailed in Table 4. Outcome data will be collected during clinically scheduled ophthalmology outpatient appointments with the CI and subjects will not be asked to attend any additional clinic appointments above those required for their clinical care. This design was used to increase the pragmatism of the study and improve subject retention throughout the duration of the study. Outcome data will not be collected for patients that withdraw from the study or deviate from the study timeline.

**Table 3 Tab4:** The scoring system used to establish participants’ knowledge of glaucoma and its management. Source: [9]

Number	Question	Scored 0	Scored 1	Scored 2	Scored 3	Max score
1	Can you tell me what you think glaucoma is?	Don’t know/ incorrect answer	Build up of pressure, raised/high pressure, nerve damage, loss of vision	Optic nerve damage, irreversible vision loss, chronic disease, slowly progressive (in own words)	NA	2
2	Can you tell me which part of the eye can become damaged with glaucoma?	Don’t know/ incorrect answer	Back of the eye	Retina	Optic nerve	3
3	Can you tell me what effect glaucoma has on vision if left untreated?	Don’t know/ incorrect answer	You go blind/you gradually go blind/ you lose vision	You get tunnel vision	NA	2
4	Can you tell me what part of vision glaucoma affects the most?	Don’t know/ incorrect answer	Visual field/field of vision/side vision	NA	NA	1
5	Is glaucoma hereditary/does glaucoma run in families?	No/don’t know	Yes	NA	NA	1
6	Do you know what investigations/tests will be carried out regularly at future clinic appointments to monitor changes in your eyes?	Don’t know/ incorrect answer	Either IOP measurement, visual field test or optic nerve examination (in own words)	Any two of the tests (in own words)	All three tests (in own words)	3
7	Do you know the name(s) of the drop(s) that has/have been prescribed for you?	Don’t know/ incorrect answer	Yes (client named the drops)	NA	NA	1
8	Do you know what the drops do?	Don’t know/ incorrect answer	Lower/reduce/control eye pressure	NA	NA	1
9	Do you know when you will need to collect your next prescription?	Don’t know/ incorrect answer	1 month/28 days	NA	NA	1

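### The knowledge survey is not protected from consultation or rehearsal of the record, which only the intervention arm holds, and is scored by the unmasked investigator who issued it

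*Protocol article*

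**What the plan says.** All of the following is in the protocol article.

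- **Outcome.** The Primary outcome section defines the endpoint as understanding and retention of knowledge, taken from a researcher-conducted survey. "The survey will be administered by the CI when participants attend" a glaucoma review clinic.
- **Record.** The Intervention description says that the chief investigator hands the record to the intervention arm after consent. It is personalised to the participant's "glaucoma diagnosis and utilised during ophthalmologic review". Intervention development describes traffic-light displays for optic disc, visual field and intraocular pressure (IOP).
- **Scoring.** Question 6 of the scoring table asks which tests will be done at future visits. One point is given for "Either IOP measurement, visual field test or optic nerve examination (in own words"), two points for any two of these and three for all three. Question 2 gives its top score of 3 for the optic nerve. Question 4 gives 1 for visual field or side vision.
- **Acknowledged limitation.** The Discussion says that the assessor is not masked, because the same person issued the record and because "clients will return with (or refer too) their record at follow-up; this increases the risk of detection bias". A second assessor was judged unworkable.

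**The concern.** Three features combine. The survey is given at the kind of visit at which the record is used. Only one arm has a record to bring. The record's three measures are the three tests that earn full marks on question 6, and they bear on questions 2 and 4. If a participant looks at the record during the survey, or the investigator has just gone through it with them, the score reflects access or recent rehearsal and not what was retained over the months since diagnosis. The effect favours the intervention arm only. An unmasked scorer adds a second route to bias where an answer needs judgement.

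The article treats priming as serious elsewhere: its Consent section adopts a post-test-only design so that participants are not alerted to the benefit of education. The Discussion admits detection bias from the unmasked assessor. It does not consider that the record itself could supply or prompt answers, and the only remedy it weighs is a second assessor. At stake is how a significant primary result could be read.

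**Working it through.** **1. The plan's sample size reproduces.** The inputs are "90 % power and 5 % significance, based on two-sided Mann–Whitney" (Sample size), a "mean two-point difference in glaucoma knowledge score between groups" (Abstract), means 7 and 9 with SD 3 (Table 2), 1:1 allocation and 20% drop-out. The standardised difference is 2/3 = 0.667.
- The two-sample t test needs 48.3 per arm.
- Dividing by the Mann–Whitney relative efficiency under normality, 3/π = 0.955, gives 48.3/0.955 = 50.6, so 51 per arm.
- Adding 20% gives 51 × 1.2 × 2 = 122.4, which matches the stated "122 (61 per group").
- Completers after 20% drop-out: 61 × 0.8 = 48.8, about 49 per arm.

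**2. Points that overlap the record.** The maxima of questions 1 to 6 are 2 + 3 + 2 + 1 + 1 + 3 = 12, which is the total open to participants not on drops. Questions 2, 4 and 6 give 3 + 1 + 3 = 7 of these.

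**3. From individual gains to a shift in the arm mean.** If a share f of the intervention arm gains g points, the mean shift is b = f × g. The documents give neither f nor g, so these are assumptions.
- A quarter of the arm gaining 2 points: 0.25 × 2 = 0.5.
- Half of the arm gaining 2 points (for example, naming three tests on question 6 instead of one): 0.5 × 2 = 1.0.
- For b = 2, the share needed is 2/3 = 67% if each gains 3 points, or 2/2 = 100% if each gains 2.

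**4. Chance of a significant result with no true difference.** The Mann–Whitney test is approximated by a t test with effective size 49 × 0.955 = 46.8 per arm. The non-centrality is (b/3) × √(46.8/2) = 1.612b.

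| Assumed mean shift b | Non-centrality | 49 per arm | Simulation, 49 per arm | 61 per arm (no drop-out) |
|---|---|---|---|---|
| 0 | 0 | 5% | 4.7% | 5% |
| 0.5 | 0.806 | 12.5% | 12.7% | 14.5% |
| 1.0 | 1.612 | 35.8% | 35.1% | 43.0% |

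The simulation used 4,000 trials with scores rounded to whole numbers and limited to 0–17.

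**5. Threshold for significance.** By the t approximation, the smallest significant difference in means at 49 per arm is 1.985 × 3 × √(2/49) = about 1.2 points. A bias well below the 2-point target therefore matters.

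**The case against.** **Open-book testing is not described.** In the Discussion sentence, bringing or mentioning the record is given as a reason why the assessor is unmasked. Use during review describes care, not the survey. The order of events at the visit could also be set out in the full protocol, which is not shown. This stands in part: a reader might infer that consultation during the survey is planned, and the article does not say so. It is left possible. Even so, the article expects the record at follow-up and describes no safeguard, although the outcome is retention.

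**The unmasked assessor is disclosed.** This stands. The unaddressed part is the record's presence at the survey and the lack of any masked scoring, neither of which requires a second assessor in clinic.

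**The bias may be small.** A reader might infer that this route alone could produce the 2-point target difference. The documents do not support that. The 3 points on question 6 are one person's maximum, not a difference in means, and step 3 of the working shows how widespread such gains would have to be. Controls are also exposed to the relevant material: both arms may be shown optic nerve and visual field images at diagnosis, are given a leaflet, and have fields and IOP measured in routine care. Many should score on question 6 unaided.

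**Scoring is mostly closed.** This stands. Wording that explicitly accepts the patient's own expression appears only in questions 1 and 6. Only questions 2 and 6 reach 3 points, and most of the rest are scored 0 or 1 against listed answers.

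**The booklet is not shown.** This also stands. The overlap is inferred from Intervention development, so it is an overlap of topics and not proof that the scored answers are printed in it.

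**Conclusion.** The point holds as a gap in how the primary outcome is protected. The article leaves open a one-sided bias, favouring the intervention, in an endpoint defined as retained knowledge, and a simple safeguard is available. Its size is unknown. The rates of about 12.5% and 36% show what average shifts of 0.5 and 1 point would do to the planned test. They rest on assumed shifts, SD 3, 49 completers per arm and no true effect, and they do not estimate this trial's bias. Nothing here shows that participants will read from the record or that a positive result would be spurious. A positive result would, however, be harder to read as retention. The sample size is unaffected.

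**What to change.** 1. Give the survey at the start of the visit, before the record is opened or discussed, with the record closed and out of sight. Use the same script, without prompting, in both arms.
2. Write answers verbatim on a form that carries only the trial number. Where existing staff unaware of allocation are available, have them score all forms against the table, masked to arm. The trial administrator holds the allocation sequence and so would not qualify. The article does not state whether the statistician is masked, so this must be confirmed first.
3. For surveys already taken, report how many preceded the change and compare the arms separately before and after it, keeping all randomised participants. Do not drop surveys at which the record was in view: only one arm has a record, so this would be a one-sided exclusion after randomisation, and for past surveys it would rest on the unmasked investigator's recall.

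The cost is a slight change to clinic order, a form to complete and a scoring session. No second assessor is needed in clinic. Notes taken by the unmasked investigator will not remove all prompting or transcription bias, and the limitations text should say so.

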## Trial status

Recruitment to the HOPE Glaucoma study began in June 2013. Recruitment is ongoing, with 85 % of the sample size achieved. The study is anticipated to reach the recruitment target of 122 participants in September 2014.

## Abbreviations

CI: chief investigator
COAG: chronic open-angle glaucoma
HRQOL: health-related quality of life
IOP: intraocular pressure
MD: mean deviation
OHT: ocular hypertension
PDS: pigment dispersion syndrome
PEXF: pseudoexfoliative glaucoma
SAP: standard automated perimetry
SG: suspected glaucoma
VFQ-25: National Eye Institute Visual Functioning Questionnaire – 25
